## Methods

### Study design

Evaluation of the CFM intervention follows a cluster randomized controlled trial design. Following a baseline survey, we used stratified randomization to allocate 74 villages to either the intervention or control arm on a 1:1 basis. Approximately four to six months after intervention delivery, we will conduct an endline survey in the study villages among all eligible consenting caregivers of children < 5 years old (at the time of intervention delivery), along with environmental sampling in a sub-set of households to measure fecal contamination. Effectiveness of the intervention will be assessed on an intention-to-treat basis by comparing the proportion of households in intervention and control villages that report safely disposing of their child’s feces (either by the caregiver disposing of the child’s feces into the latrine or the child using the latrine) the last time the child defecated. A process evaluation will be conducted during intervention delivery to provide targeted feedback to the implementing team and to measure intervention fidelity and reach. We will also conduct in-depth interviews post implementation with the Gram Vikas mobilizers and a sub-set of caregivers who participated in the intervention to elicit feedback on what they liked and did not like about the intervention and to identify recommendations for future implementations.

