### Inclusion/exclusion criteria

Villages were eligible for inclusion if they met the following criteria: completed MANTRA program, village size is between 35 to 250 households, 75% of households have access to a latrine, community water tank is functional, village has its own *Anganwadi* center (government-run daycare and preschool center), and Gram Vikas has no programming planned in the village during the study period. The WASH related criteria are meant to ensure most eligible households in the trial villages already have access to water and a latrine so that caregivers have an enabling environment to perform the safe CFM practices being promoted. Moreover, Gram Vikas plans to continue addressing WASH infrastructure needs in villages with lower coverage and functionality, and as such desired the CFM intervention to be tailored towards villages that did not require this additional infrastructure investment. The remaining criteria aim to mitigate issues related to logistics (smaller villages may have no or very few eligible households with young children, larger villages require more inputs), spillover (an *Anganwadi* center used by multiple villages could lead to spread of intervention messaging), and exogenous influences (other Gram Vikas programs could influence effectiveness of the CFM intervention). In addition, eligible villages had to be accessible throughout the year and not previously engaged in formative research activities or piloting of data collection tools.

For the baseline survey, all households with a latrine and at least one child < 5 years old residing in the home were eligible for inclusion. For the endline survey, all households with a latrine and at least one child who was < 5 years old at the time of intervention delivery will be eligible for inclusion. This ensures all households that could have been exposed to the intervention will be attempted for the endline survey. We will only engage participants age 18 years or older for all research activities, except for hand-rinse samples which will engage children < 5 years old upon caregiver consent.

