
### Study outcomes and measures

The primary outcome is a binary measure of *safe disposal of child feces,* as defined by the WHO/UNICEF Joint Monitoring Programme for Water Supply and Sanitation (JMP). The updated JMP definition describes safe disposal as encompassing two distinct behaviors based on the last time the child defecated: 1) child used the toilet/latrine or 2) caregiver put/rinsed the child’s feces into the toilet/latrine [36]. JMP defined safe disposal of child feces is assessed in both the baseline and endline cross-sectional samples. The primary caregiver of the child < 5 years old (< 5 years at time of survey for baseline; < 5 years at time of intervention delivery for endline) in the household is asked “The last time [NAME OF CHILD] defecated, where did [NAME OF CHILD] defecate?” If the caregiver reports anything except “in latrine” then the following question is asked “Where was [NAME OF CHILD]‘s feces disposed?” A child’s feces are deemed safely disposed if the child defecated in the latrine or if the caregiver disposed of the child’s feces into the latrine.

We recognize that the primary outcome is subject to response bias since it is measured using caregiver self-report. However, asking a respondent to report on the “last time” a behavior took place rather than the “usual” practice is a more robust approach, as demonstrated for other sanitation practices such as latrine use [37]. This is also the approach taken by the JMP. If a caregiver reports “do not know” for the two questions assessing safe disposal, however, then the caregiver will be asked to report on the “usual” practice instead. We anticipate this case to be rare based on previous research conducted in Odisha [26].

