### Data and sample collection

#### Trial

Baseline and endline data collection will be carried out by a team of enumerators and supervised by a local research manager. All team members will be fluent speakers of the local language Odia. For baseline data collection, we conducted a week-long training followed by several days of pilot-testing in non-trial villages, and the same will be done before endline. Throughout the training, team members provide critical feedback on both data collection logistics and the survey tool, especially with regard to question construction (ease of comprehension, colloquial phrasing, etc.), Odia translation, skip patterns, and more (see Supplemental File 2 for the baseline survey tool). For endline data collection, the team will not be informed of village intervention status, but it may be possible for them to infer due to the visible components of the intervention or survey questions related to the intervention.

During both baseline and endline data collection, the enumerator teams will attempt to survey all eligible households within the study village. The target respondent is the primary caregiver of the child < 5 years old. If the primary caregiver is not available then a secondary caregiver is asked to participate. After confirming eligibility and obtaining verbal consent from the participant, the enumerator will conduct the survey. Following the survey, the enumerator will ask to observe the household’s latrine and bathing room and complete a structured spot-check.

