### Data analysis

#### Trial

We will employ an intention-to-treat analysis for all primary comparisons between the intervention and control arms. The effect of the intervention on JMP defined safe disposal will be assessed using a log-binomial model, which will yield the prevalence ratio of post-intervention safe disposal among intervention households relative to control households. We will use generalized estimating equations (GEE) with robust standard errors to account for village-level clustering and will adjust for stratified randomization by geo-demo group and baseline prevalence of safe disposal. If any relevant variables are found to be substantially imbalanced between the two arms at baseline then an additional model will adjust for these variables. All adjusted and unadjusted models will be reported. GEE will also be used to examine the impact of the intervention on secondary outcomes using the appropriate distribution and link function for each specific secondary outcome. If there is variation in the level of household participation in intervention activities, then a per-protocol analysis will be conducted to better measure the efficacy of the intervention on safe disposal behavior change under ideal conditions. A sensitivity analysis will also be conducted to examine differences in safe disposal between those households that were surveyed at baseline and endline compared to those only surveyed at endline. Lastly, we will employ mediation analysis [47] to examine which behavioral factors the CFM intervention influenced and which behavioral factors were then linked to changes in safe CFM behaviors, including safe disposal and child latrine training.

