A notable factor that has already influenced this study and will continue to is the COVID-19 pandemic. Field activities were paused for a six-month period after baseline data collection as the novel coronavirus spread globally and the Gram Vikas team concentrated their efforts on Odisha’s pandemic response. Being a more isolated area, Gajapati district continues to have a low caseload while Ganjam district, once a viral hotspot, has drastically slowed its infection rate [48, 49]. It is possible the situation could change and research activities will again need to halt, potentially affecting implementation or endline data collection. The COVID-19 pandemic also influenced intervention design where community-wide behavior change strategies were purposefully not considered to safeguard against viral spread. However, as the intervention is meant only for a sub-set of the community (i.e. households with a child < 5 years), such strategies were already not prioritized. Gram Vikas will implement the intervention following preventative measures such as mask-wearing and keeping physical distance from participants. It is this ‘COVID conscious’ version of the intervention that will be evaluated but we do not anticipate such additional measures to impede the behavior change strategies. Finally, there is a potential for the external context of the pandemic to influence caregiver’s CFM practices from a heightened risk perception and promotion of related-behaviors like handwashing. During the pause period we conducted phone interviews among trial villages to assess how COVID-19 impacted WASH practices. While we found the pandemic impacted daily life [50], we found no evidence of impact on CFM or sanitation behaviors [51]; any impact would also equally affect both intervention and control arms.

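### The sensitivity analysis for the open endline sample compares repeat with endline-only households and states no arm contrast, so it cannot show whether the effect holds in households identified before allocation

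*Protocol article*

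**What the plan says.** All references are to the protocol article.

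- **Order of events (Study design):** "Following a baseline survey, we used stratified randomization to allocate 74 villages to either the intervention or control arm on a 1:1 basis".
- **Endline eligibility (Inclusion/exclusion criteria):** "all households with a latrine and at least one child who was < 5 years old at the time of intervention delivery". The stated reason is "This ensures all households that could have been exposed to the intervention will be attempted for the endline survey". Having been surveyed at baseline is not required.
- **Sampling (Study outcomes and measures; Data and sample collection, Trial):** "JMP defined safe disposal of child feces is assessed in both the baseline and endline cross-sectional samples". At both rounds, "the enumerator teams will attempt to survey all eligible households within the study village".
- **Primary estimate (Data analysis, Trial):** the "prevalence ratio of post-intervention safe disposal among intervention households relative to control households", from a log-binomial GEE model analysed by intention to treat.
- **Sensitivity analysis (same section):** to "examine differences in safe disposal between those households that were surveyed at baseline and endline compared to those only surveyed at endline".

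The other additional analyses in that section are adjustment for imbalanced baseline variables, a per-protocol analysis by level of participation, and mediation. None of them separates households by when they were identified.

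**The concern.** Households surveyed at baseline were identified before anyone knew the village's arm. Endline-only households join the sample after an allocation that is open to participants and investigators. The useful question is whether the intervention effect is the same when the later entrants are left out.

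The stated comparison answers a different question, namely whether households with different survey histories differ in safe disposal. The two groups were not formed by randomisation and can differ for ordinary reasons, the age of the child above all. A difference could be misread as evidence of bias, and the absence of one as reassurance. Neither would bear on the primary prevalence ratio.

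**Working it through.** **1. The protocol's own figure.** Inputs from Sample size, Trial: 40.7% against 55.7%, 9 households per village, 10% loss, ICC 0.103, 80% power, significance level 0.05 (two-sided assumed).

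- Individuals per arm: (1.960 + 0.842)² × (0.407×0.593 + 0.557×0.443) / 0.15² = 170.3.
- Households per village after loss: 9 × 0.9 = 8.1. Design effect: 1 + 7.1 × 0.103 = 1.731.
- Villages per arm: 170.3 × 1.731 / 8.1 = 36.4, rounded up to 37. This agrees with the protocol, and the prevalence ratio 0.557/0.407 = 1.37 also agrees. The point below changes neither figure.

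**2. What the stated contrast can detect.** Assume arms of equal size and 70% of endline households surveyed at both rounds. All rates below are assumed for illustration. The stated contrast is taken as the mean of the two arms in repeat households minus the mean of the two arms in endline-only households.

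| Scenario | Repeat: control / intervention | Endline-only: control / intervention | Stated contrast | Arm effect, repeat | Arm effect, all |
|---|---|---|---|---|---|
| A. Uniform effect | 40.7 / 55.7 | 40.7 / 55.7 | 48.2 − 48.2 = 0 | 15 | 15 |
| B. Effect only in later entrants | 48.2 / 48.2 | 33.2 / 63.2 | 48.2 − 48.2 = 0 | 0 | 0.7×0 + 0.3×30 = 9 |
| C. Stable effect, later entrants lower | 40.7 / 55.7 | 30.7 / 45.7 | 48.2 − 38.2 = 10 | 15 | 15 |

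The contrast gives the same answer for A and B, the two cases it would need to tell apart. It signals a difference in C, where the effect in points is unchanged. The arm effect in repeat households separates B from both A and C.

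**3. Why a gap unrelated to bias is plausible.** Endline-only households include those whose first child was born between baseline and delivery. That window contains a pause: "Field activities were paused for a six-month period after baseline data collection". Study setting and population reports that 84.7% of the 40.7% safe disposal came from the child using the latrine directly: 0.847 × 40.7 = 34.5 points, leaving 6.2 points from caregiver disposal. Among children not using the latrine, safe disposal is therefore 6.2 / (100 − 34.5) = 9.5%. Households with a very young child could thus report less safe disposal in both arms. This supports the direction only. The protocol gives neither age-specific rates nor the make-up of the endline-only group.

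**4. Precision of an arm comparison in repeat households.** Let f be the repeat share, which the protocol does not give. Then m = 8.1f, and the effective number per arm is n = 37m / (1 + (m − 1) × 0.103). Power = Φ{[0.15√n − 1.960√(2×0.482×0.518)] / √(0.407×0.593 + 0.557×0.443)}.

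| f | m | Power for 15 points | Difference detectable at 80% |
|---|---|---|---|
| 1.0 | 8.10 | 80.0% | 15.0 |
| 0.9 | 7.29 | 77.8% | 15.4 |
| 0.8 | 6.48 | 75.0% | 15.9 |
| 0.7 | 5.67 | 71.7% | 16.6 |
| 0.5 | 4.05 | 62.2% | 18.5 |

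These figures ignore variation in cluster size, so actual power would be somewhat lower. At f = 0.7 about 8.1 × 0.3 = 2.4 endline-only households remain per village, so an interaction estimate will be imprecise.

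**The case against.** The strongest reply is that this is one condensed sentence in a paragraph about the intervention effect. It does not say that the arms are pooled, and an analysis plan not shown here might fit the primary model by group. That is possible. Still, the sentence names a specific comparison, and that comparison contains no arm contrast. If a by-arm analysis is meant, saying so costs a few words.

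A second reply is that the protocol already limits selective entry. Endline is an attempted census, eligibility rests on having a latrine and a child under five at delivery, and the endline team is not told the village's status, although it may infer it. This stands, and it limits how far the point can be taken. A reader might infer that the primary analysis is biased or should be restricted to baseline households. The protocol does not support that: villages were the randomised units, and analysing all eligible endline households by intention to treat is sound.

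A reader might also treat the whole interval from baseline to endline, at least 10 to 12 months (six-month pause plus four to six months of follow-up), as the period in which new households enter. It is not. A birth after delivery does not make a household eligible, so entry through a first birth closes at delivery. Nor can endline-only households be assumed to be mostly new parents. They also include households missed or refusing at baseline, in-migrants, and those that gained a latrine, in unknown proportions.

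Finally, a refit in repeat households is not fully protected, because those households must also be reached and consent at endline, after open allocation. That is correct and belongs in the interpretation.

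**Conclusion.** The point holds as a fault in a stated sensitivity analysis. As worded, the comparison cannot tell an effect shared by all households from one carried by households entering after allocation (a stated contrast of 0 in both, under the assumed rates), and it can show a difference (10 points) when the effect is stable. No other analysis in that section fills the gap.

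The primary estimate, the sample size and every stated figure are unaffected, and nothing here shows that recruitment bias has occurred. It is tempting to put a large figure on the age-related gap. For example, 40.7 − 9.5 gives about 31 points, but only if every endline-only child is a non-user of the latrine and the comparison group sits at the overall average. The protocol supports neither condition, so the size of the gap is left open. The illustration rests on assumed rates, a 70% repeat share and equal arms. The power figures rest on an assumed repeat share and equal cluster sizes.

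**What to change.** Before endline data are analysed, reword the sensitivity analysis in Data analysis, Trial, as three items:

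1. The primary GEE model, with its existing adjustments, refitted in households surveyed at both baseline and endline.
2. An arm-by-survey-status interaction in the full endline sample, reported as an estimate with a confidence interval and not judged by its p-value, since it will be imprecise. Give the arm comparison within each group as a difference as well as a ratio. In scenario C the difference is 15 points in both groups, while the prevalence ratios are 55.7/40.7 = 1.37 and 45.7/30.7 = 1.49, so an interaction under the log link would not be exactly null.
3. The number of endline-only households in each arm.

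Add a sentence saying that item 1 addresses differential entry after allocation but not differential response at endline.

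The cost is a change of wording and two further model fits on data the trial already plans to collect, provided households can be linked across rounds, which the stated comparison also needs. The drawback is lower precision in the subset: about 72-78% power for 15 points if 70-90% of endline households are repeats, before cluster-size variation. That is acceptable for a sensitivity analysis. The primary analysis stays as it is.

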#### Environmental sampling

We will also use GEE models with robust standard errors that account for village level clustering to analyze if the intervention had an impact on environmental contamination based on collected environmental sampling data from drinking water and hand rinse samples. Separate models will be created for drinking water contamination and hand contamination. Separate models will also be run to analyze the binary outcome of prevalence of *E. coli* as well as the continuous outcome of log *E. coli* concentration. *E. coli* concentration data will be log transformed prior to analysis. If any baseline imbalance is found in contamination levels between intervention and control villages, then this will be adjusted for in final models.

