Secondary outcomes include household fecal contamination measured by *E. coli* enumeration from collected drinking water and hand rinse samples; other CFM practices such as material used to handle child feces; child latrine use among children up to age 10; psychosocial factors related to safe disposal and child latrine training measured by RANAS questionnaires; and caregiver received social support for CFM. Both the RANAS and social support questionnaires were developed based on qualitative formative research and revised through cognitive interviews. The social support items measure informational, instrumental, and emotional support pertaining to CFM and were adapted from several validated metrics [38–42]. These secondary outcomes are also assessed at both baseline and endline.

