#### Environmental sampling

For environmental sampling, the sample size will be based on logistical feasibility to ensure that samples can be processed in the laboratory on the same day of collection. As a result, only villages that have a driving time from the laboratory of two to three hours or less will be included in sample collection. Additionally, sample collection will be limited to a maximum of 15 households per village. In villages that have more than 15 households with children < 5 years, households for sample collection will be randomly selected. The procedure followed at endline will be similar to the procedure followed at baseline.

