## Village selection and random allocation

We randomly selected 74 villages from a sample frame of 501 MANTRA villages in Ganjam and Gajapati districts. Following baseline data collection, author [name] used stratified randomization to allocate villages into intervention or control arm on a 1:1 basis (Fig. 1). A computer-based random number generator was used to complete the allocation. Villages were categorized into one of five distinct geographic-demographic (‘geo-demo’) groups, which served as the stratification variable to ensure balance on a wide range of factors. Villages in each ‘geo-demo’ group have a distinct set of characteristics with regard to their geography (coastal, hilly, tableland, etc.), predominant religion and caste, village size, market access and other characteristics. The ‘geo-demo’ groups mostly align with the ‘block’ level administrative unit (a district subdivision), with several blocks falling under each group. As such, three of the ‘geo-demo’ groups are located entirely in Ganjam district while the remaining two are in Gajapati district. We used replacement re-randomization to ensure balance on two a priori specified variables: number of eligible households per village and village-level baseline reported safe disposal of child feces. We used the Mann-Whitney U Test to test if the distribution of villages on these two variables was not significantly different between the study arms. We also used an independent samples t-test to test if the mean baseline reported safe disposal of child feces was not significantly different between the study arms. The a priori balance criteria were met with the first randomization attempt. Participants and study investigators will not be blinded to village treatment assignment.

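### The E. coli models adjust for baseline contamination only if an imbalance is found; prespecifying that adjustment, with geo-demo group, would remove discretion and may gain some precision

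*Protocol article*

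**What the plan says.** Under Data analysis, Environmental sampling, the *E. coli* outcomes are modelled as follows: "We will also use GEE models with robust standard errors that account for village level clustering". Water and hands are modelled separately, and each is analysed as presence and as log concentration, which makes four models. The baseline rule is: "If any baseline imbalance is found in contamination levels between intervention and control villages, then this will be adjusted for in final models". No test, threshold or measure of imbalance is given, and geo-demo group is not mentioned in that paragraph.

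Under Data analysis, Trial, the safe-disposal model "will adjust for stratified randomization by geo-demo group and baseline prevalence of safe disposal", without any condition. Imbalance there leads only to a supplementary analysis: "If any relevant variables are found to be substantially imbalanced between the two arms at baseline then an additional model will adjust for these variables". Results with and without adjustment are to be reported.

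Three other places bear on the point:
- Village selection and random allocation: the geo-demo grouping has five levels, "which served as the stratification variable to ensure balance on a wide range of factors". The re-randomization balance criteria were eligible households per village and baseline safe disposal. Contamination was not among them.
- Study outcomes and measures, on the secondary outcomes, which include *E. coli*: "These secondary outcomes are also assessed at both baseline and endline".
- Sample size, Environmental sampling: "only villages that have a driving time from the laboratory of two to three hours or less will be included in sample collection". At most 15 households per village are sampled, and the number of villages is not stated.

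**The concern.** The two analysis paragraphs apply different logic to the same design. For safe disposal, the stratification factor and the baseline outcome are always in the model, and imbalance only adds a further model. For *E. coli*, imbalance decides what the final model is. With no criterion, two analysts could reach different final models from the same baseline data, separately for each of the four models.

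The statistical objection is that the value of a baseline covariate depends on its correlation with the endline outcome, not on whether randomization left a chance difference. Making adjustment depend on that difference forgoes the gain in trials where the arms look alike.

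Precision matters here because *E. coli* is the only laboratory-measured outcome in the list, the primary outcome is self-reported, and sampling is sized by feasibility in a subset of villages. Baseline samples are already part of the design, so the covariate needs no further collection.

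**Working it through.** **Plan's own figure.** No sample size or power is stated for *E. coli*. The trial calculation does reproduce. With 40.7% against 55.7%, two-sided 5% (sidedness assumed) and 80% power, individual randomization needs 170.3 per arm. With 9 × 0.9 = 8.1 households per village and ICC 0.103, the design effect is 1 + 7.1 × 0.103 = 1.7313. Then 170.3 × 1.7313 / 8.1 = 36.4, so 37 villages per arm, as stated. I use its ICC and cluster size below as borrowed inputs; they belong to another outcome.

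**Gain from always adjusting.** For village means with baseline-endline correlation r, the residual variance is multiplied by 1 − r² and the standard error by √(1 − r²). If the unadjusted comparison had 80% power, adjusted power is Φ(2.80/√(1 − r²) − 1.96). The documents do not give r, so a range is shown.

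| r | 1 − r² | SE ratio | SE reduction | Power (unadjusted 80%) |
|---|---|---|---|---|
| 0.1 | 0.99 | 0.995 | 0.5% | 80.4% |
| 0.2 | 0.96 | 0.980 | 2.0% | 81.6% |
| 0.3 | 0.91 | 0.954 | 4.6% | 83.6% |
| 0.5 | 0.75 | 0.866 | 13.4% | 89.9% |
| 0.7 | 0.51 | 0.714 | 28.6% | 97.5% |

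**Which r is plausible.** The relevant r is between observed village means, which household noise attenuates. If baseline and endline means are equally reliable, observed r = true village-level r × reliability, where reliability = m × ICC / (1 + (m − 1) × ICC). With ICC 0.103:
- m = 9: 0.927 / 1.824 = 0.51.
- m = 15 (the sampling cap): 1.545 / 2.442 = 0.63.

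At this ICC, observed r cannot exceed 0.51 to 0.63, so 0.7 is out of reach. With 9 households, r = 0.5 needs a true correlation of 0.5 / 0.508 = 0.98. A true correlation of 0.5 gives observed r of about 0.25 and an SE reduction of 1 − √(1 − 0.25²), about 3%. A household-level simulation with true r 0.7 and ICC 0.1 gave a 3-8% reduction. A higher *E. coli* ICC would raise these limits.

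**What the conditional rule does.** A village-level simulation (4,000 runs per scenario, five strata) represented the rule as adjusting when a baseline test gives p < 0.05. That threshold is my assumption. Baseline then entered the model in about 3-5% of trials. Power at 20 villages per arm, with no stratum variance:
- r = 0.5: 77.8% unadjusted, 78.4% conditional, 88.1% always adjusted.
- r = 0.2: 77.8%, 77.7% and 78.7%.

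With an assumed 20% of variance between strata (20 or 37 villages per arm), null rejection was 3.1-3.5% under the conditional rule without strata. With strata and baseline in the model it was 4.7-5.5%. No scenario showed inflation from the rule.

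**Small samples.** In null GEE simulations with 24 to 50 villages, adjusted models with plain robust z-tests rejected about 9-15%. A Kauermann-Carroll correction with a t reference brought this to 5.2-5.9% (continuous outcome). A separate simulation with 24 or 40 villages gave 5.0-6.5% with the same correction.

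**The case against.** Several points on the other side have force.

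- *Strata.* A reader might infer that the *E. coli* models leave out the stratification factor. The document does not establish this. The paragraph is silent, its opening can be read as continuing the Trial paragraph, and a condensed article may leave a covariate list to a fuller plan. What stands is that naming the factor would remove the doubt.
- *Data-driven choice.* A reader might infer that the model is picked in light of the results. Baseline was complete and villages were allocated when the article was written, so imbalance can be settled before any endline sample exists. What stands is discretion over what counts as imbalance.
- *The word any.* Read literally, some difference almost always exists, so the rule comes close to always adjusting. The low adjustment rate in the simulation comes from an assumed test. This is fair, and it shows that the rule spans nearly always to hardly ever.
- *Stability of contamination.* Activities halted for six months after baseline, the samples are cross-sectional, and the hand rinse may come from the youngest child, an older child or the caregiver. All of this could lower r.
- *The remedy has a price.* In one simulation with 24 villages, true r of 0.3 and no stratum variance, adding baseline and four stratum terms slightly raised the estimator's standard deviation (0.203 against 0.196). Adjusted models with plain robust z-tests also reject too often. This stands, and it is why the fix includes a small-sample correction.

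**Conclusion.** The conditional rule is stated explicitly, is inconsistent with the protocol's treatment of its primary outcome, and is worth changing. Its consequences are moderate: some lost precision, possibly conservative tests if strata differ and are not modelled, and avoidable discretion, all for secondary outcomes.

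The size is unknown. It is about 1-5% of the standard error for observed r of 0.1-0.3, and about 13% at r = 0.5 only if the *E. coli* ICC is well above 0.103 or village contamination is very stable. A reader might take the 29% at r = 0.7 as a realistic gain; the borrowed ICC does not support that. A reader might also infer that the rule produces false positives; the simulations showed none from it. The over-rejection above belongs to plain robust z-tests with few villages and matters because the remedy adds covariates.

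These conclusions rest on an assumed range for r, an ICC taken from a different outcome, assumed stratum variance, and assumed numbers of sampled villages.

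**What to change.** Replace the conditional sentence with wording such as: all four *E. coli* models (water and hands, prevalence and log concentration) will adjust for geo-demo group and for the village-level baseline value of the same outcome, regardless of observed imbalance; unadjusted results will be reported alongside. A village-level summary works even where endline households differ from baseline households, provided the village was sampled at both rounds. The article already says the endline procedure will be similar to baseline.

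Because only a subset of the 74 villages is sampled, specify a small-sample corrected robust standard error (for example Kauermann-Carroll) with a t reference on villages minus parameters. Its performance for the two binary models should be checked before it is fixed, since the main support here is for the continuous outcome.

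The change is to analysis wording only and needs no extra samples or visits. It uses five degrees of freedom (four stratum terms and one baseline term) and brings little or no precision gain if the baseline-endline correlation is low.
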